##### **4.2. Per Protocol Set (PPS)**

The PPS will consist of subjects from the FAS, excluding cases with protocol deviations related to study methods or concomitant therapies, including:

- Violation of inclusion criteria
- Violation of exclusion criteria
- Protocol deviations (e.g., failure to complete two scheduled exercise tests).

##### **4.3. Handling of Subjects**

The Principal Investigator will make decisions regarding the handling of enrolled subjects. If any issues arise concerning subject handling, the matter will be resolved through consultation with the Lead Statistician.

#### **5. Plan for Analysis of Subject Breakdown and Overall Exposure Status**

##### **5.1. Breakdown of Subjects**

The following items will be summarized, showing frequencies and percentages. The results will be presented in figures and tables.

- Enrolled cases
- Cases included in the analysis for the primary endpoint
- Cases included in the analysis for each secondary endpoint
- Cases with violations of inclusion criteria
- Cases with violations of exclusion criteria
- Discontinued cases
- Dropouts
- Completed cases

## **6. Efficacy Analysis**

### **6.1. Primary endpoint**

Patient satisfaction calculated by Likert-Scale. Patient satisfaction, assessed using a Likert scale were compared between the two groups. Mean changes from baseline to the final follow-up were analyzed using unpaired t-tests.

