#### **4.4 Bias**

Adaptive randomization method will be applied to reduce intervention bias. Due to the nature of the intervention, blinding is not feasible, and thus the trial will be conducted with an open-label design.

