## **9. Statistical Analysis**

### **9.1 Number of Registered Cases**

A total of 50 cases will be assigned to either the ePRO response group or the non-response group.

Basis: The number of participants was determined based on the number that can be registered within the set research period by the research group. Therefore, no power analysis was conducted.

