### **1.1. Primary endpoint**

Patient satisfaction calculated by Likert-Scale

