### **1.5. Sample size**

Target Sample Size: 50 subjects (25 subjects  $\times$  2 groups)

Because this was a pilot randomized controlled trial, formal sample size calculations were not performed.

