### **2.4. Significance Level and Confidence Interval**

A two-sided significance level of 5% will be used for hypothesis testing. When calculating confidence intervals, a two-sided 95% confidence interval will be applied.

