## **2.7. Data Handling**

In principle, data handling decisions will be made by the Principal Investigator. If questions or uncertainties arise, the final decision will be made in consultation with the Lead Statistician. The handling of missing values and variable transformations is outlined below:

- **Missing Data:** No special statistical imputation methods will be applied to missing data. An unpaired t-test will be performed on complete data excluding missing data.
- **Outlier Data:** The handling of outlier data will be determined by the Data Handling Committee (comprising the Principal Investigator and the Lead Statistician).
- **Variable Transformation:** If variable transformations (e.g., square root or logarithmic transformations) are applied, details will be documented in the "Analysis Results Report."

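### The unpaired t-test on change in satisfaction (SAP 6.1 and 6.2) is valid, but adjusting for the baseline score would usually be more precise with 25 patients per arm and would remove the conditional error from baseline imbalance

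*Combined protocol and SAP*

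**What the plan says.** The primary endpoint in SAP 1.1 is "Patient satisfaction calculated by Likert-Scale"; neither the number of items nor the score range is given. SAP 6.1 states the analysis: "Mean changes from baseline to the final follow-up were analyzed using unpaired t-tests". SAP 6.2 repeats that sentence for the secondary questionnaire scores. SAP 2.7 confirms the method for incomplete data: "An unpaired t-test will be performed on complete data excluding missing data".

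SAP 1.5 sets the size: "Target Sample Size: 50 subjects", 25 per group, and says that "formal sample size calculations were not performed". Protocol 9.1 explains that the number is what could be enrolled in the study period: "Therefore, no power analysis was conducted". SAP 2.4 nevertheless plans formal tests: "A two-sided significance level of 5% will be used for hypothesis testing".

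Three other places bear on the point.
- Protocol 9.2 lists a multivariate analysis beside unpaired t-tests, with no endpoint, model or covariates. Protocol 7.2 lists paired t-tests and logistic regression. The SAP carries none of these into its primary analysis.
- Protocol 4.4 describes the allocation: "Adaptive randomization method will be applied to reduce intervention bias". It names no balancing factor, and it says the trial is open-label.
- Protocol 4.2 and SAP 3 place the first outcome questionnaire after randomisation and the second at the fifth visit.

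**The concern.** Subtracting the baseline score fixes its slope on the final score at 1. With equal SDs at the two times the actual slope is rho, which is below 1, so subtraction over-corrects. Two things follow. The comparison is noisier than it need be, and when the arms differ at baseline, part of that difference passes into the estimate with the opposite sign.

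Both matter more in a small trial. Recruitment is capped by feasibility, so the efficiency of the analysis is one of the few things still open to choice. With 25 per arm, appreciable baseline differences are also common. The baseline score is already being collected, so using it better needs no new data.

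**Working it through.** **The plan's own figure.** There is nothing to reproduce. The total of 50 is a feasibility number with no effect size, SD, correlation or power behind it.

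**Inputs.** From the documents: 25 per arm (SAP 1.5) and two-sided alpha 0.05 (SAP 2.4). Assumed: equal SDs at both times (set to 1), rho of 0.3, 0.5, 0.7 and 0.9, an illustrative true effect of 0.7 SD, and no dropout.

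**1. Variance.** Per patient, Var(change) = 2(1 − rho) and Var(ANCOVA) = 1 − rho². The large-sample ratio is therefore (1 + rho)/2. Estimating one slope from N = 50 multiplies the ANCOVA variance by about 1 + 1/(N − 4) = 1 + 1/46 = 1.022.

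| rho | Var(change) | Var(ANCOVA) | ratio | ratio × 1.022 |
|---|---|---|---|---|
| 0.3 | 1.40 | 0.91 | 0.65 | 0.66 |
| 0.5 | 1.00 | 0.75 | 0.75 | 0.77 |
| 0.7 | 0.60 | 0.51 | 0.85 | 0.87 |
| 0.9 | 0.20 | 0.19 | 0.95 | 0.97 |

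**2. Power for a 0.7 SD effect.** This uses the noncentral t with noncentrality 0.7/√(variance × 2/25), on 48 df for the change score and 47 df for ANCOVA with the 1.022 factor. At rho 0.5, for example, the standard errors are √(1.00 × 0.08) = 0.283 and √(0.75 × 1.022 × 0.08) = 0.248.

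| rho | change-score t-test | ANCOVA |
|---|---|---|
| 0.3 | 54% | 71% |
| 0.5 | 68% | 79% |
| 0.7 | 88% | 92% |

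At rho 0.9 both are close to 100%. A t-test on the final score alone has variance 1 and so 68% power at every rho. The change score only equals that at rho 0.5, and falls below it when rho is smaller.

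**3. Baseline imbalance.** The standard error of the baseline mean difference is √(2/25) = 0.283 SD. Under simple randomisation a difference beyond ±0.3 SD has probability 2[1 − Φ(0.3/0.283)] = 29%. Given a baseline difference D, the expected error of the change-score estimate is rho·D − D = −(1 − rho)D. For D = 0.283 this is −0.20, −0.14, −0.08 and −0.03 SD at rho 0.3, 0.5, 0.7 and 0.9. Baseline adjustment subtracts the estimated slope times D, so the expected error is zero.

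**4. Simulation.** In 40,000 simulated trials of 25 per arm at each rho, with normal data and no effect, the change-score test rejected in 4.8% to 5.0% and ANCOVA in 4.9% to 5.1%. Averaged over all trials, both estimates were within 0.003 SD of the truth. Among trials with a baseline difference above one standard error, the mean error of the change score was about −0.30, −0.22, −0.13 and −0.04 SD; that of ANCOVA was at most 0.005 SD in size.

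**5. Cost of more covariates.** With baseline plus two indicators for disease group (HF, AF, CAD), the variance factor is about 1 + 3/44 = 1.068. If disease group explains nothing further, the ratios become 0.69, 0.80, 0.91 and 1.01.

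**The case against.** The strongest case against is that nothing here is an error. The t-test on change is a legitimate analysis, SAP 1.5 calls the trial a pilot, and no power target exists to be missed. That stands: this is a recommendation about efficiency and conditional error. It does not make the point idle, because the SAP plans a 5% test and a confidence interval, and the better use of baseline is almost free.

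It can also be said that Protocol 9.2 already allows for adjustment. The multivariate analysis there is undefined and not tied to the primary endpoint, so it does not settle the matter.

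A reader might infer more than the documents support in four respects.
- **That ANCOVA wins at any rho below 1.** This is a large-sample statement. At N = 50 the net gain at rho 0.9 is about 3% with one covariate, and it vanishes with three if disease group is not prognostic.
- **That the slope is certainly below 1 because a rating is bounded.** The slope is rho × SD(final)/SD(baseline), and neither SD nor the scale range is given. It is plausible but not established.
- **That the test is conservative and its interval too wide because it omits the allocation factors.** This requires covariate-adaptive allocation on factors that predict the outcome. Protocol 4.4 says only that the method is adaptive. Questionnaire type is assigned before randomisation, but nothing says that allocation is balanced on it. No size can be put on such an effect.
- **That any baseline imbalance is pure chance.** The first questionnaire follows open-label randomisation, so answers may already reflect knowledge of the arm. That would affect ANCOVA and change scores alike, and adjustment alone would not cure it.

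**Conclusion.** The point holds as a matter of precision and conditional error, not validity. If rho is between 0.3 and 0.7, adjusting for baseline alone saves about 34% to 13% of the variance at 25 per arm; at 0.9 it saves about 3%. The conditional shift from a one-standard-error baseline difference runs from 0.20 SD down to 0.03 SD over the same range and is removed by adjustment.

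These figures rest on equal SDs, approximate normality, complete follow-up and an assumed rho. The variances and shifts do not depend on the effect size; the power figures are for 0.7 SD only. The change is worth making, but the planned test would not be wrong without it. Its full benefit depends on a baseline measured before the patient knows the allocation.

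**What to change.** In SAP 6.1, and in 6.2 for each score compared between arms, make the main analysis a linear model (ANCOVA) of the visit-5 score on arm and the baseline score of the same scale. Add any factor actually used in the allocation, and name those factors in Protocol 4.4. Report the adjusted mean difference with its 95% confidence interval. Keep the unpaired t-test on change as a supportive analysis. Bring SAP 2.7 and Protocol 7.2 and 9.2 into line with the chosen model.

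In Protocol 4.2 and SAP 3, have the outcome questionnaires completed after consent but before the allocation is revealed.

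The cost is a change of wording, one model statement and one degree of freedom out of 48, plus one for each further term. The downside is small: almost no gain if rho is near 0.9, and a slight loss if several non-prognostic terms are added as well.

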## **7. Efficacy Evaluation**

### **7.1 Efficacy Evaluation Indicators**

### **7.2 Methods for Evaluating, Recording, and Analyzing Efficacy Evaluation Indicators**

ePRO and questionnaire data will be collected using electronic devices and stored in the Smart-Pro (tentative name) system on servers contracted by Chubu Electric Power Co., Inc. The data will be displayed on a dedicated web interface to improve patient satisfaction through result viewing during consultations between physicians and patients. Researchers will extract data from the server and manage it as research data. The data will be matched with patient background and medical data, and changes in the utilization of ePRO will be analyzed. Planned analyses include paired t-tests and logistic regression analyses.

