### **9.2 Analysis of Results**

Analyses will be performed using multivariate analysis, unpaired t-tests, etc.

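### The primary and secondary scores are tested as raw change from baseline with no adjustment for their own baseline: a valid test, but less precise than ANCOVA on data already collected

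*Combined protocol and SAP*

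**What the plan says.** SAP 6.1 (primary endpoint, satisfaction on a Likert scale) states: "Mean changes from baseline to the final follow-up were analyzed using unpaired t-tests". SAP 6.2 repeats the sentence for the PSQ score and for Quality of Information. SAP 2.7 names the same test under missing data: "An unpaired t-test will be performed on complete data excluding missing data". None of these sections names a covariate.

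The protocol mentions other methods without assigning them. Section 9.2 says "Analyses will be performed using multivariate analysis, unpaired t-tests, etc". Section 7.2 says "Planned analyses include paired t-tests and logistic regression analyses". Neither states an endpoint, a model or a baseline term.

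The target is 50 patients, 25 per group (SAP 1.5), set by feasibility. SAP 1.5 says "formal sample size calculations were not performed", and protocol 9.1 says "Therefore, no power analysis was conducted". SAP 2.4 nevertheless plans formal testing: "A two-sided significance level of 5% will be used for hypothesis testing".

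Protocol 4.2 and SAP 3 place the first outcome questionnaire after randomisation and the last at the fifth visit. Protocol 4.4 says the trial is open-label.

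**The concern.** A change score fixes the slope of the final score on baseline at 1. With equal SDs at the two times the true slope is rho, which is below 1. On a bounded satisfaction score, patients near the top have little room to rise. The change score then over-corrects for baseline, and if rho is below 0.5 it is less precise than ignoring baseline altogether. ANCOVA uses the same two measurements and estimates the slope from the data.

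Two things are at stake. The interval for the only primary comparison is wider than it needs to be, in a trial whose size was fixed by feasibility. The estimate also moves with any chance difference at the start: if the ePRO arm begins higher by luck, regression to the mean counts against it, and the reverse if it begins lower.

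**Working it through.** **Inputs from the documents.** 25 per group (SAP 1.5), two-sided 5% and 95% intervals (SAP 2.4), unpaired t-test on change (SAP 6.1, 6.2). No power, effect size or SD stands behind the 50, so there is no figure of the plan's own to reproduce.

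**Assumptions.** The documents give no rho and no SD. I take equal SDs at baseline and visit 5 (SD = 1) and rho from 0.3 to 0.7, with 0 and 0.9 as outer values.

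**Precision.**
- Variance per patient: change score 2(1 − rho); ANCOVA 1 − rho². The ratio ANCOVA/change is (1 + rho)/2.
- Cost of estimating the slope at N = 50: multiply the ratio by 1 + 1/(50 − 4) = 47/46.
- Patients' worth of information lost: 50 × (1 − ratio).
- 95% CI half-width: t × √(2 × variance/25), with 48 df for change and 47 df for ANCOVA. The ANCOVA variance includes the 47/46.

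| rho | Change var. | ANCOVA var. | Ratio | Lost of 50, nominal | Ratio × 47/46 | Lost of 50, small-sample | Half-width, change v ANCOVA |
|---|---|---|---|---|---|---|---|
| 0 | 2.00 | 1.00 | 0.50 | 25.0 | 0.511 | 24.5 | – |
| 0.3 | 1.40 | 0.91 | 0.65 | 17.5 | 0.664 | 16.8 | 0.67 v 0.55 SD |
| 0.5 | 1.00 | 0.75 | 0.75 | 12.5 | 0.766 | 11.7 | 0.57 v 0.50 SD |
| 0.7 | 0.60 | 0.51 | 0.85 | 7.5 | 0.868 | 6.6 | 0.44 v 0.41 SD |
| 0.9 | 0.20 | 0.19 | 0.95 | 2.5 | 0.971 | 1.5 | – |

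The gain vanishes where (1 + rho)/2 × 47/46 = 1, that is at rho = 92/47 − 1 ≈ 0.96. Simulating 20,000 trials of 25 v 25 with normal scores gave losses of 16.4, 11.8 and 6.6 patients at rho 0.3, 0.5 and 0.7, close to the formula.

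The difference detectable with 80% power, change v ANCOVA, is 0.96 v 0.78 SD (rho 0.3), 0.81 v 0.71 (0.5) and 0.63 v 0.58 (0.7).

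**Chance imbalance.** The baseline difference between arms has SD √(2/25) = 0.28 and exceeds 0.3 SD in either direction in about 29% of trials. Given an observed difference, the change-score estimate shifts by (1 − rho) times that difference, in the opposite direction. For 0.3 SD this is 0.7 × 0.3 = 0.21 SD at rho 0.3, 0.15 at 0.5 and 0.09 at 0.7. The simulated slopes were −0.69, −0.50 and −0.30 for the change score and about 0 for ANCOVA. With no true effect, both estimators averaged within 0.002 SD of zero over all simulated trials.

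**Bounded scale, as illustration only.** The SAP does not describe the Likert scale. All settings below use an assumed 5-category scale.

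| Assumed setting | Latent rho | Power, change v ANCOVA |
|---|---|---|
| 30% in top category at baseline, latent shift 0.8 SD | 0.4, 0.6, 0.75 | 52 v 74%, 64 v 82%, 78 v 90% |
| Same ceiling, shift 0.4 SD | 0.4, 0.6, 0.75 | 18 v 26%, 24 v 32%, 37 v 42% |
| Symmetric, 10% in top category, shift 0.8 SD | 0.75 | 91 v 95% |

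In the 0.8 SD settings with a ceiling, type I error was 4.5 to 5.5% for both methods. The direction is constant, but the size depends on the scenario.

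**The case against.** **The planned test is valid.** This stands. A reader might infer that the change-score t-test is biased or inflates false positives. Neither the theory nor the simulations support that. It is unbiased over repeated randomisation, and the shift described above is conditional on the imbalance that happens to occur.

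**The patient count is not a fact about this trial.** This also stands. A reader might take a fixed number of wasted patients from the table. The documents give no rho, and the loss runs from nearly half the sample at rho 0 to almost nothing at rho 0.9. SAP 2.7 and 4.1 also drop patients without data, so the analysed number, and with it the loss, may be smaller.

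**It is a pilot, so power matters less.** Partly fair. The gain that counts is interval width, about 18%, 12% and 7% at rho 0.3, 0.5 and 0.7, and the last is modest. But the SAP still tests at 5%, and a tighter estimate is useful from a pilot too.

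**Protocol 9.2 already allows multivariate analysis.** It does, so the plan is not silent on modelling. But no endpoint or covariate is named, and SAP 6.1, the more specific text, names only the t-test.

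**Adaptive randomisation (protocol 4.4) handles imbalance.** Not for this variable. The outcome questionnaire is answered after randomisation, so its score is not available when patients are allocated.

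**A baseline taken after open-label allocation is a poor covariate.** This is a real limit, but it does not favour the existing plan. If disclosure moves the first answer by d and leaves visit 5 untouched, the change-score estimate is off by the full d, and ANCOVA by only the slope times d. A pure reporting shift that lasted unchanged to visit 5 would instead cancel in the change score and not fully in ANCOVA. The remedy for either case is an earlier questionnaire.

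**Conclusion.** The point holds as an efficiency recommendation. SAP 6.1 and 6.2 specify no adjustment for the outcome's own baseline, and nothing elsewhere in the documents supplies one. ANCOVA would be more precise at any rho below about 0.96 with 50 patients and equal SDs, and it would remove the dependence of the estimate on chance baseline differences.

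The size rests on assumed values: for rho 0.3 to 0.7, about 17 down to 7 patients' worth of information out of 50. The power figures illustrate one assumed scale and should not be read as a forecast; the gain is smaller with a smaller shift or less ceiling. The documents do not support calling the planned test invalid or its estimate biased overall.

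**What to change.** In SAP 6.1 and 6.2, replace the test with wording such as: *The visit-5 score will be compared between arms by linear regression on arm, with the baseline score of the same scale as covariate. The adjusted mean difference, its 95% confidence interval and two-sided p-value are the main result. The unpaired t-test on change from baseline is supportive.* Change SAP 2.7 so that the complete-case rule refers to this model. In protocol 9.2, replace the open mention of multivariate analysis with the same model, and reconcile protocol 7.2 with it.

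Where still possible, have patients complete the first outcome questionnaire before allocation is disclosed. If that is too late, state the timing as a limitation of both analyses.

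The analysis change costs wording and one degree of freedom, with no new data, visits or patients. Moving the questionnaire is a small change of procedure. If the data are already locked, ANCOVA can still be reported and explained as a deviation under protocol 9.6.

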### **6.2. Secondary endpoint**

1. Assessment of well-being, patient preferences for shared decision-making using questionnaires.
2. Qualitative assessment of ePRO monitoring in ePRO group.

The changes in Patient Satisfaction Questionnaire (PSQ) score and Quality of Information (QoI) related to treatment and prognosis were compared between the two groups. Mean changes from baseline to the final follow-up were analyzed using unpaired t-tests.

### **6.3. Exploratory endpoint**

Factors associated with improved patient satisfaction in ePRO group

For qualitative data, the changes from before to after the intervention were compared.

## **7. Safety analysis**

### **7.1. Adverse Events**

The incidence and number of cases of adverse events will be summarized, and the occurrence rate along with its 95% confidence interval will be calculated. The two-sided 95% confidence interval will be determined using an exact method based on the F-distribution.

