### **5.3 Discontinuation Criteria**

The principal investigator or sub-investigators will discontinue the study for a subject if any of the following conditions are identified after subject registration:

- (1) An adverse event occurs, and the principal investigator or sub-investigators determine that the study should be discontinued.
- (2) The subject requests to withdraw from the study.
- (3) It is determined that the subject is inappropriate for inclusion in the study.
- (4) It becomes evident that the necessary observations and tests cannot be conducted due to the subject's circumstances.
- (5) Any other reason where the principal investigator or sub-investigators judge that the collection of questionnaire data should be discontinued.

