## **8. Safety Evaluation**

### **8.1 Adverse Events (AE)**

The time required to answer the questionnaire is approximately 5 minutes each time, which may cause mental distress or time constraints.

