### **8.3 Procedures for Collecting, Recording, and Reporting AE/SAE**

Not anticipated.

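### SAP 7.1 plans an adverse-event rate with an exact 95% interval, but the protocol gives no procedure for collecting adverse events, so a low or zero rate could not be told apart from non-ascertainment

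*Combined protocol and SAP*

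**What the plan says.** SAP 7.1 commits to a quantitative safety result: "The incidence and number of cases of adverse events will be summarized", together with an occurrence rate. It also names the interval method: "The two-sided 95% confidence interval will be determined using an exact method based on the F-distribution". It does not say whether the rate is pooled or by arm, on which analysis set it is based, or over what period.

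The protocol section headed "Procedures for Collecting, Recording, and Reporting AE/SAE" has as its whole content "Not anticipated". Protocol 8.2, on serious events, gives the same answer. Protocol 8.1 does name a possible harm: "The time required to answer the questionnaire is approximately 5 minutes each time, which may cause mental distress or time constraints". SAP 1.4 repeats that sentence and adds no method of recording.

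The itemised data in protocol 4.2 cover patient background, blood tests and investigations. Protocol 4.3.1 and 4.3.2 name the sources: the ePRO survey, the outcome questionnaires, the patients themselves for background information, and the electronic medical record. None of these sections lists adverse events, deaths or hospitalisations as an item. Adverse events otherwise appear as a ground for stopping a subject's participation in protocol 5.3 ("An adverse event occurs, and the principal investigator or sub-investigators determine that the study should be discontinued") and in assurances of medical care in 2.3 and 8.4. Protocol 11 provides for no monitoring or auditing.

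**The concern.** A statement that events are not expected is a view about their frequency. It does not define an event or say who asks, at which visit, or on what form. The SAP nonetheless treats the count as a binomial numerator over a known denominator. An exact interval for a proportion has its stated coverage only if every patient in the denominator was assessed for the event.

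At stake is what the trial can say about safety. Followed as written, the plan could yield a rate at or near zero with a formal interval attached, and a reader could not tell how much of that reflects the absence of events and how much the absence of a procedure.

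The silence on arm adds to this. Only ePRO patients complete the disease-specific questionnaire at every visit, so a pooled rate would dilute any burden that falls mainly on them. Noticing may also differ by arm, because only in the ePRO group does the physician review a symptom report with the patient, and the trial is open-label (protocol 4.2 and 4.4).

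**Working it through.** The documents state no expected adverse-event rate, so there is no planned figure to reproduce. Two checks are possible.

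**1. What the planned interval would show.** Inputs: 50 subjects, 25 per group (SAP 1.5); two-sided 95% level (SAP 2.4); exact F-distribution method (SAP 7.1), which is the Clopper-Pearson interval. With zero events the upper limit reduces to 1 − 0.025^(1/n).

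- n = 50: 1 − 0.025^(1/50) = 7.1%.
- n = 25: 1 − 0.025^(1/25) = 13.7%.
- With one recorded event, the F-distribution form gives 0.05% to 10.7% for 1/50 and 0.1% to 20.4% for 1/25.

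The F-distribution and beta-quantile forms agree.

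**2. What the interval leaves out.** Let p be the true proportion of patients with an event and s the share of those who are recorded. The documents give neither, so the values below are assumptions shown as a range. The recorded count is then binomial with probability p × s, and the data carry information on the product only. Three quite different situations with n = 50 show this:

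| True p | Share recorded s | p × s | Expected count | P(zero recorded) = (1 − p × s)^50 |
|---|---|---|---|---|
| 5% | 100% | 5% | 2.5 | 0.95^50 = 7.7% |
| 10% | 50% | 5% | 2.5 | 7.7% |
| 20% | 25% | 5% | 2.5 | 7.7% |

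The three rows give the same distribution of results, so the trial could not distinguish them.

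Coverage of the true proportion, by exact binomial sums over the counts whose interval includes p, with n = 50:

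| True p | s = 100% | s = 50% | s = 25% | s = 10% |
|---|---|---|---|---|
| 20% | 97% | 57% | 10% | 0.3% |
| 10% | 97% | 92% | 72% | 40% |
| 5% | 99% | 100% | 100% | 100% |

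With p = 20% and s = 10%, no event would be recorded in 0.98^50 = 36% of trials. When the true rate is as low as 5%, under-recording does little damage to coverage at this sample size. The problem is material only if the true rate is appreciable and capture is poor, and the plan provides no means of knowing whether that is so.

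**The case against.** The best defence is that this is a low-risk pilot. The intervention is a questionnaire of about five minutes, all patients attend five outpatient visits, the medical record is a stated data source, an event can lead to discontinuation, and medical care is promised if one occurs. Safety is not among the endpoints in SAP 1.1 to 1.3. Most of this stands, and it limits the point in four ways.

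- A reader might infer that a near-zero rate would be an artefact. The documents do not show that; a truly low rate is plausible.
- A reader might infer that nobody would ask patients about harms. Contact with patients is planned throughout; what is missing is a documented, systematic procedure.
- A reader might infer that the foreseen burden would go wholly unmeasured. The secondary outcomes include well-being and a qualitative evaluation of the monitoring among ePRO patients. The content of the latter is not given, so it may or may not cover burden. It would not cover controls.
- A reader might infer that unrecorded deaths or admissions explain missing satisfaction data. The documents give no expected number of such events, and SAP 5.1 already counts discontinuations and dropouts, although it does not promise reasons.

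Nor is the exact method at fault, or its result deceptively narrow: 7.1% and 13.7% are wide limits, and any proportion depends on ascertainment. None of this supplies the missing procedure. Low risk can justify light collection or no rate at all, but not an interval on data that the plan does not say how to collect. Part of the SAP between 7.1 and 8.3 is not in the public text and cannot be judged; protocol 8.3, the designated place, is present and contains no procedure.

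**Conclusion.** SAP 7.1 and protocol 8.3 are inconsistent. As written, a low or zero adverse-event rate could not be distinguished from non-ascertainment, and its interval (upper limit 7.1% for 0/50, 13.7% for 0/25) would describe sampling error only. How far the interval could mislead depends on the true rate and the share recorded, both unknown: across the assumed range, coverage runs from nominal or better down to almost nil. The conclusion that the two sections must be reconciled does not rest on those assumptions. It is a minor point, because it affects the safety statement alone; the primary satisfaction comparison and the sample size are untouched.

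**What to change.** Choose one of two routes.

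1. **Report without a rate.** Delete the incidence and its interval from SAP 7.1. List the events that were noted, by arm, and state that harms were not systematically assessed. This is a wording change and remains possible after follow-up has ended.

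2. **Collect, then report.** Replace the present content of protocol 8.3 with the same ascertainment in both arms: death and unplanned hospitalisation during follow-up, taken from the electronic medical record that is already read. If follow-up is still open, add one distress or burden item, asked of both arms at visit 5 only. State the analysis set and period in SAP 7.1 and tabulate by arm with exact intervals. The cost is two record fields and at most one tablet item.

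If a burden item is also asked at each ePRO completion, summarise it descriptively within the ePRO arm and do not compare it between arms. Up to five opportunities to report against one would build in differential ascertainment.

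Protocol 4.7 ends the study period on March 31, 2024, and SAP 6 describes its analyses in the past tense, so follow-up may be over; the documents do not settle this. If it is, the first route and the record extraction remain available, but the tablet item does not.
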